## Abstract

**Introduction:**

Diet is an important factor in managing glycemic control in type 1 diabetes (T1D). Reducing carbohydrate intake may be important for stabilizing blood glucose levels in certain groups of patients with T1D. There are few studies examining the effects of a low carbohydrate diet in patients with T1D. The aim of this study is to investigate the effects of carbohydrate intake on glucose control in adults with T1D.

**Materials and methods:**

Adults with T1D (*N* = 54) and inadequate glycemic control (HbA1c ≥ 7.5%; 58 mmol/mol) were randomized in a cross-over design to a moderate carbohydrate diet (30 percent of total energy from carbohydrates) versus a traditional diabetes diet (50 percent of total energy from carbohydrates) for 4 weeks with a between wash-out period of 4 weeks. Masked continuous glucose monitoring was used throughout the study to evaluate effects on mean blood glucose levels, time-in-range, hypoglycemia, hyperglycemia, and glycemic variability. Diabetes treatment satisfaction, hypoglycemic confidence, and physical activity were measured using questionnaires during different phases of the trial. HbA1c, blood lipids, blood pressure, and ketone levels were also measured. The primary endpoint is the difference in mean blood glucose level between the diet periods. Study completion is anticipated during winter 2022.

**Discussion:**

The study seeks to increase knowledge about the effects of dietary carbohydrate intake on glycemic control and other health parameters in patients with T1D. If beneficial effects on mean blood glucose level without elevated risk of hypoglycemia or ketoacidosis are shown, a moderate carbohydrate diet may be a treatment option for people with T1D that have unsatisfactory blood glucose levels.

**Clinical Trials Registration:**
www.clinicaltrials.gov, ID: NCT03400618.

## Introduction

1.

Good glycemic control in patients with type 1 diabetes (T1D) is related to decreased risk of complications and lower mortality (1–3). Mortality remains considerably higher in patients with T1D which could be decreased significantly if more patients reached target blood glucose levels (3, 4).

Diet is essential to achieve good glycemic control (5, 6). Mediterranean diet, Dietary Approaches to Stop Hypertension (DASH), and vegetarian dietary patterns are recommended by American Diabetes Association clinical practice guidelines for people with diabetes (5). Certain foods and food groups have been shown to have protective effects on cardiovascular risk (7–13). Carbohydrate counting is a method widely used in clinical practice, although the effectiveness of this method on glycemic control has been questioned (14–17).

Reducing dietary carbohydrates may be of importance for stabilizing glucose levels in certain groups of persons with T1D. If the insulin dose is incorrect by 20%, a greater effect on blood glucose will likely occur with greater carbohydrate content in the meal. Also, even during controlled conditions it is hard to predict an exact insulin dose making it difficult for patients to calculate the exact insulin dose to the amount of carbohydrates. This is because of the intraindividual variation in the uptake of insulin in the body of all available insulin sorts (18, 19). There are also many other factors that have an effect, such as physical activity during the past 24 h (20) making insulin doses hard to standardize.

Few studies have examined the effects of lower carbohydrate diets in patients with T1D and results are conflicting. A systematic review (21) examined the effects of LCDs (<45% of total energy) on glycemic control in eight studies of adults and children with type 1 diabetes. The studies were heterogenic and of small size and the results conflicting. In a large European observational study, they could see a trend that a lower intake of total carbohydrates was associated with lower HbA1c (22). This was also reported in another observational study in Denmark where higher intake of carbohydrates was associated with higher HbA1c in persons with T1D (23). A Finnish observational study reported that adherence to LCD was associated with lower BMI, lower variability of blood glucose measurements and lower diastolic blood pressure (24). A small study (*n* = 11) showed that a ketogenic diet (carbohydrate <55 g/day) was associated with excellent HbA1c levels [35 ± 4 mmol/mol (5.3 ± 0.4%)] and little glycemic variability, although it was also associated with dyslipidemia and a high number of hypoglycemic episodes (25). The studies that have shown beneficial effects on glycemic control with LCD are small (26–29) and/or not randomized and lacking control groups (29, 30).

The aim of this study is to analyze the effects of a moderate carbohydrate diet (30 percent of total energy) compared with a traditional diabetes diet (50 percent of total energy) on glycemic control and risk of ketoacidosis in patients with T1D.

## Methods and analysis

2.

### Design and randomization

2.1.

This is a randomized, open-label, cross-over clinical trial being conducted at four Swedish diabetes specialty centers. Enrolment commenced in March 2018 and study completion is expected during winter 2022. Patients were randomized 1:1 to either moderate carbohydrate or traditional diabetes diet for 4 weeks with an intermittent wash-out period of 4 weeks followed by the other intervention diet for 4 weeks. Expected study duration for each participant was 14–16 weeks, including a run-in period of 2–4 weeks. Eligible participants were identified from each diabetes center registry, and patients were invited to participate by written correspondence or telephone. Randomization was performed on site using a centralized web system with random permuted blocks of varying sizes. Each patient was assigned a unique coded subject ID at randomization.

### Study participants

2.2.

Adults with T1D and HbA1c levels ≥58 mmol/mol (7.5% DCCT standard) were included in the study. Other inclusion and exclusion criteria are given in Table 1. A total of 69 subjects were screened and 54 randomized and included in the study. A flow diagram of participant recruitment during the cross-over study according to CONSORT is shown in Figure 1.

**Table 1 tab1:** Inclusion and exclusion criteria for participation in the study.

Inclusion criteria
1. Type 1 diabetes
2. Adults 18 years or older
3. Written informed consent
4. HbA1c ≥ 58 mmol/mol (7.5% DCCT standard)
**Exclusion criteria**
1. Pregnancy or planned pregnancy during the study period
2. Severe cognitive dysfunction or other disease as determined by the physician
3. Inability to comply with study diet (excluding foods common to each diet such as wholegrains, beans, lentils, fruit, and vegetables because of personal preferences)
4. Other disease
5. Diabetes duration <1 year
6. Planned change in diabetes treatment (e.g., commencing insulin pump or CGM) during the study period

**Figure 1 fig1:**
[figure not shown]
Flow diagram of participants during the cross-over study according to CONSORT.

The study was approved by the regional ethics committee of Gothenburg, Sweden (No. 473–17). All subjects received written and verbal information about the study and gave their written informed consent before inclusion.

### Dietary interventions

2.3.

Dietary interventions consisted of moderate carbohydrate diet: (30 percent of total energy from carbohydrates) and traditional diabetes diet with low glycemic index (50 percent of total energy from carbohydrates). Macronutrients in each diet are presented in Table 2.

**Table 2 tab2:** Macronutrients in the two intervention diets.

	Moderate carbohydrate diet	Traditional diabetes diet with low glycemic index
Carbohydrates (% of total energy)	30–40	50–60
Fat (% of total energy)	40–50	25–35
Protein (% of total energy)	20	15–20

Moderate carbohydrate diet included meat, fish, shellfish, eggs, vegetables, root vegetables, vegetable proteins, olive−/rapeseed oil, nuts and seeds, avocado, and margarine. Includes less sugar, bread, cereals, potatoes, rice, and pasta. Carbohydrates were mainly wholegrains and carbohydrates with low glycemic index.

Traditional diabetes diet included lean meat, fish, shellfish, vegetable proteins, beans, lentils, pasta, potatoes, rice, and grains. The recommended bread was wholegrain and with low glycemic index. Generally, it included a lot of vegetables and root vegetables as well as fruit and berries with low glycemic index (e.g., apple, orange, and pears), olive−/rapeseed oil, nuts and seeds, avocado, margarine, etc. This diet is in line with general nutrition recommendations.

Both diets were individualized by a dietitian to fit each subject in terms of energy (kcal) and macronutrient (carbohydrate, fat, and protein) intake and in line with current public nutrition guidelines. At clinical visits and each telephone contact, patients were encouraged to maintain diet in accordance with the protocol.

All diet material used in the study were made by a dietitian and included several recipes, different meal examples with carbohydrate content, whole day menus, and ideas for suitable foods, snacks, and meals suitable for each diet intervention. The same material was used at all 4 study sites but were individualized by the local dietitian depending on individual energy demands and personal preferences of participants.

All subjects recorded their food intake in a 4-days food diary at 3 times during the study. First during the run-in period to provide data for the dietitian to make the calculations and look at food preferences to be able to make the individual diet plans. To be able to measure adherence to the intervention diets the subjects were also instructed to record food intake for 4 days during the last 2 weeks of each intervention period. All food records will be calculated regarding macronutrient and energy intake by a dietitian. Protocol compliance and adherence were checked at each contact, and diet, blood glucose levels, and insulin dosages at each clinical visit.

### Continuous glucose monitoring

2.4.

All patients used a masked continuous glucose monitoring (CGM) system (Freestyle Libre Pro, Abbott Diabetes Care) during a run-in period of 2–4 weeks and then continuously for the rest of the study period for a total of 14–16 weeks. Data were collected from the CGM system at all clinical visits. Patients using CGM or Intermittent scanned Continuous Glucose Monitoring (isCGM) in their usual diabetes care continued to use this as well. Missing data from the masked CGM sensor could be replaced by data from patients regular, non-blinded CGM/isCGM device in the statistical analyses if available. All deviations such as which devices were used were carefully documented.

### Insulin adjustments

2.5.

Insulin adjustments were reviewed by a diabetes nurse or physician at the beginning of each treatment phase to ensure that participants adjusted insulin doses properly when changing diet. Clinical support was only provided at the start of each treatment phase, whereas during the evaluation period (last 14 days of each diet period) patients fully adjusted their doses on their own. Basal insulin and basal insulin dose in the insulin pump were adjusted by an algorithm primarily based on fasting blood glucose levels and overnight glucose profiles. At high fasting blood glucose levels and no tendency for nocturnal hypoglycemia the basal dose was increased in a stepwise fashion. Doses were reduced at low fasting blood glucose levels or nocturnal hypoglycemia. Glucose excursions at bedtime were also taken into consideration. For detailed algorithms see Supplementary material 1.

Patients were instructed to continue with the same strategy for dosing mealtime insulin as used in clinical practice (e.g., carbohydrate counting was continued if used). A dietitian educated patients about types of foods containing carbohydrates and provided similar support for both types of diets. A diabetes nurse or physician provided feedback at planned telephone contacts from glucose curves if apparent that mealtime doses were under- or overdosed to be taken into consideration for future mealtime insulin dosing. Patients were instructed to strive for 2-h post-meal glucose levels <10 mmol/l and pre-meal levels <7 mmol/l. Repeated glucose levels over these levels indicated that higher mealtime insulin doses were needed for that specific meal.

### Measuring blood glucose level

2.6.

Patients were advised to check glucose level (with CGM or self-monitoring of blood glucose, SMBG, depending on what the patient used) at least 4 times per day before meals and at bedtime according to diabetes guidelines and CGM system manufacturer recommendations. Patients were advised to test or check glucose levels more often if indicated. Measurement frequency from isCGM/CGM/SMBG devices were downloaded if available, otherwise patients were asked to self-report daily measurement frequency after each diet intervention period.

### Clinical measurements

2.7.

Height was measured at baseline. HbA1c was measured at baseline and before and after each diet intervention. Blood lipids (total, LDL and HDL cholesterol, apolipoproteins, and triglycerides), blood pressure, and weight were measured before and after each treatment period. Blood ketones were measured and recorded in a diary twice a week during the two diet periods by participants at home using a ketone measurement device.

### Assessment of safety

2.8.

Adverse events and severe adverse events were recorded at all visits and telephone contacts. The number of severe hypoglycemic events defined as unconsciousness due to hypoglycemia or requiring assistance were recorded. Time in low glucose values (<3.0 and <3.9) was recorded by CGM. Ketones, insulin doses, and occurrence of ketoacidosis were also recorded.

### Questionnaires

2.9.

The Diabetes Treatment Satisfaction Questionnaire (DTSQ) has been used in many diabetes therapy clinical trials and is a validated questionnaire consisting of 8 questions that measures aspects of satisfaction scored on a 7-point Likert scale, including domains of current treatment satisfaction, convenience, understanding, recommendations, and continuation of treatment (31, 32). Two separate items measure perception of hyperglycemia and hypoglycemia. Two versions were used: the DTSQs and DTSQc, where the DTSQs was used for recording current treatment satisfaction and the DTSQc for patients to retrospectively compare the two treatments. Patients completed the DTSQs before and after each diet period and the DTSQc after the last diet period.

The Hypoglycemia Confidence Scale is a validated, 9-item scale that evaluates patient confidence regarding their ability to prevent and address hypoglycemic events (33). Patients completed the questionnaire before and after each diet period at the study site. Study personnel aided with completing questionnaires if needed without influencing patient responses. Physical activity was measured at baseline and before and after each diet intervention by questionnaires and scales to calculate energy requirements for each diet. Questions included whether physical activity changed during the last 14 days and on a scale measuring physical activity from 1 to 10 as well as 24-h physical activity.

### Trial procedures

2.10.

Patients completed a total of 6 visits to the diabetes center. Visit 1 included information about the study and informed consent. Visit 2 was the start of a 2–4-week run-in period and included physical examination, start of masked CGM, instruction about recording food intake for 4 days, diet interview, and HbA1c measurement. Visit 3 included randomization and instructions from the dietitian and diabetes nurse for starting diet intervention. Patients meeting inclusion criteria, performing 2-week masked CGM, and completing food recording were randomized. Fasting blood samples, weight, and blood pressure were measured and questionnaires completed. Telephone follow-up was performed during the diet intervention at 1-, 4-, 7-, and 14-days post-intervention. At visit 4, the first intervention was completed and CGM data, fasting blood samples, weight, and blood pressure measured and questionnaires answered. At visit 5 the second intervention began with the same procedures followed as during the first intervention. At visit 6 the second intervention was completed, and data collected as with visit 4. Enrolment schedule, interventions, and measurements according to Standard Protocol Items: Recommendations for Intervention Trials (SPIRIT) requirements are shown in Figure 2. A checklist according to SPIRIT 2013 is also provided. See Supplementary material 2. All measurements and questionnaires were recorded in an eCRF-system (Medicase AB). The study was monitored by the Department of Molecular and Clinical Medicine, Institution of Medicine, Sahlgrenska Academy, University of Gothenburg.

**Figure 2 fig2:**
[figure not shown]
Enrolment schedule, interventions, and measurements according to Standard Protocol Items: Recommendations for Intervention Trials (SPIRIT) requirements. AE, adverse event; CGM, continuous glucose monitoring; SAE, severe adverse event.

### Evaluation period and endpoints

2.11.

Evaluations were performed during the last 2 weeks of each treatment phase when patients did not receive any clinical support regarding diet or insulin adjustments. The primary endpoint is the mean blood glucose level measured by CGM during the evaluation period. Secondary endpoints are the differences between the two diet interventions in standard deviations of blood glucose levels, time above range, time in range, weight, total, LDL, and HDL cholesterol, triglycerides, total insulin dose, DTSQs, DTSQc, and Hypoglycemia Confidence Score. All endpoints are shown in Table 3.

**Table 3 tab3:** Endpoints in the study.

Primary endpoint
Difference in mean blood glucose level between the two diet periods^1^
**Secondary endpoints**
The difference in standard deviation of blood glucose levels between the two diet periods^1^
The difference in time above range between the two diet periods (above 10.0 mmol/l and above 13.9 mmol/l respectively) ^1^
The difference in time in range (5.5–10.0 mmol/l and 3.9–10.0 mmol/l respectively) between the two diet periods^1^
The difference in weight between the two diet periods
The difference in total cholesterol between the two diet periods
The difference in LDL cholesterol between the two diet periods
The difference in HDL cholesterol between the two diet periods
The difference in triglycerides between the two diet periods
The difference in total insulin dose between the two diet periods
The difference in DTSQc score at the end of the study between the two diet periods
The difference in DTSQs scores between the two diet periods
The difference in hypoglycemia confidence scores between the two diet periods

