**Other exploratory endpoints**
The difference in MAGE between the two diet periods^1^
The difference in HbA1c between the two diet periods
The difference in apolipoproteins between the two diet periods

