The primary efficacy analysis will be the analysis of the mean difference in mean glucose levels measured by CGM during the last 2 weeks of the treatment period between moderate carbohydrate diet and traditional diabetes diet on the Full Analysis Set. The treatment effect will be estimated using linear mixed effects models for normally distributed variables as described above.

All statistical tests will be two-sided and conducted at the 5% significance level. To account for multiple testing, a sequential testing procedure will be employed. If a test gives a significant result at the 0.05 significance level, the total probability mass of 0.05 will be transferred to the next endpoint in the test sequence until a nonsignificant result is achieved. All these significant tests will be considered confirmatory. *p*-values and confidence intervals of remaining endpoints will be presented descriptively.

Statistical analyses will be performed using SAS statistical software version 9.4. A Statistical Analysis Plan with a detailed description of all planned analyses will be completed and signed before the database is locked. Once all study data are collected and entered, the database will be reviewed for completeness, accuracy, and consistency. At a formal Clean File meeting the database will be declared locked, and the analysis can start.

The target sample size was set to 52 subjects to detect a clinically relevant difference in mean glucose levels of 1 mmol/l between treatments, assuming a within subjects’ standard deviation of 2.5 mmol/l, paired *T*-test, 80% power, significance level *α* = 0.05. The standard deviation was estimated on data from the GOLD cross-over trial (34).

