The study period of 12 weeks and active intervention periods of each 4 weeks was planned to be relatively short since we wanted participants to comply to changes in diets and advanced study related procedures including food diaries, ketone levels and masked CGM. The main goal of the trial is to evaluate if different carbohydrate content in diet influences glucose levels. Moreover, the use of masked CGM-data for key endpoints capturing differences in glucose patterns continuously gives an opportunity to capture the current glucose effects during each treatment period. Hence, the current study will show if a lower content of carbohydrates in diet *per se* leads to more stable glucose levels and if ketone levels are influenced. However, it is important to notice that if the intervention diet leads to improved glucose control it will be essential to evaluate whether such a diet can be kept over long time periods with sustained effects on glucose control.

In summary, this study seeks to increase knowledge about the effects of dietary carbohydrate intake on glycemic control and other health parameters in patients with T1D. If beneficial effects on mean blood glucose level without elevated risk of hypoglycemia or ketoacidosis are shown, a moderate carbohydrate diet may be a treatment option for people with T1D that have unsatisfactory blood glucose levels. If shown to have no beneficial effects, this study will hopefully increase knowledge among healthcare professionals whether moderately decreasing carbohydrate intake is safe when educating patients about diet.

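### Glucose stability is measured only in absolute units (SD and MAGE), so the listed endpoints cannot separate a proportional fall in glucose from a change in relative variability

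*Protocol article*

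**What the plan says.** The protocol article treats stability as a question of its own. The abstract's rationale is that "Reducing carbohydrate intake may be important for stabilizing blood glucose levels in certain groups of patients with T1D". The abstract's methods say masked CGM was used "to evaluate effects on mean blood glucose levels, time-in-range, hypoglycemia, hyperglycemia, and glycemic variability", which names variability separately from the mean. The Discussion (section 3) promises an answer on whether eating less carbohydrate in itself "leads to more stable glucose levels and if ketone levels are influenced".

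Section 2.11 sets the primary endpoint: "The primary endpoint is the mean blood glucose level measured by CGM during the evaluation period". It presents Table 3 as the full list of endpoints. Two entries there measure variability:

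- secondary: "The difference in standard deviation of blood glucose levels between the two diet periods"
- exploratory: "The difference in MAGE between the two diet periods"

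Table 3 has no coefficient of variation (CV, SD divided by mean). The mixed model in section 2.12 has fixed terms for diet, period and sequence and a random subject term. Mean glucose is not a covariate for SD or MAGE.

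**The concern.** SD and MAGE are both in mmol/l. If a patient's whole glucose profile shrinks by some percentage, both shrink by that percentage, although the pattern of fluctuation relative to the level is unchanged. The trial is sized to find a difference in the level itself, so this is a situation it should expect to face.

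A significant fall in SD alongside a fall in the mean would have two readings. Glucose may have become steadier relative to its level, or it may simply have become lower in proportion. No endpoint in Table 3 tests which. The primary endpoint is unaffected; what is at stake is the separate stability conclusion that the Discussion says the trial will deliver.

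**Working it through.** **The plan's own figure.** Section 2.12 gives 52 subjects for a 1 mmol/l difference, SD 2.5 mmol/l, paired t-test, 80% power, alpha 0.05 (two-sided). The normal approximation is n = (2.5 × (1.960 + 0.842) / 1)² ≈ 49.1, so 50. The exact noncentral t calculation gives 52, with 80.8% power. The figure therefore reproduces with 2.5 read as the SD of the paired difference. Only the 1 mmol/l and the 52 are carried forward.

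**Inputs that the document does not give (assumed).** CV of glucose within a patient 30-45%; starting mean 9-12 mmol/l; SD of the within-patient difference in glucose SD 0.5-1.0 mmol/l.

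**Algebra for a 1 mmol/l fall from mean m.**

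- Proportional fall, x → x(m − 1)/m: SD falls by SD/m = CV × 1 mmol/l, which is 0.30-0.45 mmol/l for CV 30-45%, whatever m is. As a share this is 1/m: 1/12 to 1/9, or 8-11%. MAGE falls by the same share. CV does not change. Example: mean 10, CV 36%: SD 3.60 → 3.24; 3.24/9 = 36%.
- Constant shift, x → x − 1: SD and MAGE do not change. CV becomes SD/(m − 1). Same example: 3.60/9 = 40%.

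**Check on one simulated 14-day trace (illustrative only).**

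| | Mean | SD | MAGE | CV | Time 3.9-10.0 | Time >10.0 | Time <3.9 |
|---|---|---|---|---|---|---|---|
| Start | 10.14 | 3.23 | 6.68 | 31.8% | 46.0% | 51.6% | 2.5% |
| Minus 1 mmol/l | 9.14 | 3.23 | 6.68 | 35.3% | 53.5% | 41.0% | 5.5% |
| Scaled to same mean | 9.14 | 2.91 | 6.02 | 31.8% | 56.9% | 39.8% | 3.3% |

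Each of the three time-in-band measures moves in the same direction in both cases. They respond to level and spread together and do not test relative variability.

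**Chance that the SD endpoint is significant after a purely proportional fall.** Paired t-test, n = 52, two-sided 0.05, noncentrality = (drop / SD of differences) × √52. For example, 0.30/1.0 × 7.211 = 2.16, which gives 0.565.

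| CV (SD drop, mmol/l) | SD of differences 0.5 | 0.75 | 1.0 |
|---|---|---|---|
| 30% (0.30) | 0.989 | 0.808 | 0.565 |
| 36% (0.36) | 0.999 | 0.924 | 0.721 |
| 40% (0.40) | >0.999 | 0.965 | 0.808 |
| 45% (0.45) | >0.999 | 0.989 | 0.889 |

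Under a constant shift the true SD difference is zero, and the probability is the test's alpha of 5%.

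**The case against.** **Absolute spread suits the rationale.** The Introduction (section 1) argues that a given percentage error in the insulin dose moves glucose more when the meal holds more carbohydrate. That concerns the size of excursions in mmol/l, which SD and MAGE measure. If smaller post-meal peaks are what lowers the mean, dividing by the mean removes part of the effect. This stands: a lower absolute SD is a legitimate meaning of stability, so SD should stay.

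**CV has the mirror-image weakness.** It rises under a constant shift with identical excursions. This also stands. It rules out replacing SD with CV, or letting CV alone decide.

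**The listed endpoints already describe level, spread and tails, and CV is the ratio of two of them.** This is true, and it is why the change is cheap. But no difference in CV is pre-specified, and calculating one after seeing the SD result is weaker evidence.

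A reader might also infer more than the document supports:

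- *That any fall in the mean lowers SD and MAGE.* It does not; a constant shift leaves both unchanged. Nothing in the article shows which pattern will occur.
- *That SD is the next confirmatory test after the primary.* Section 2.12 says only that "If a test gives a significant result at the 0.05 significance level, the total probability mass of 0.05 will be transferred to the next endpoint", and it does not give the order. Being first among the secondary endpoints in Table 3 is not a stated place in the test sequence. Nor is a rejection for SD a false positive: if SD falls in proportion, it has truly fallen. Only its interpretation is open.
- *That a lower SD will be reported as better stability.* The article sets no rule for interpreting a fall in SD. Its stated clinical conclusion depends on mean glucose without more hypoglycemia or ketoacidosis.

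The unseen analysis plan may add CV. The point concerns Table 3, which the article presents as complete.

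**Conclusion.** The point holds in a limited form. The article promises an answer on stability but lists only absolute measures of it, without adjustment for the level that the trial is designed to change. A proportional 1 mmol/l fall would lower SD by 0.30-0.45 mmol/l with relative variability unchanged. Across the assumed ranges this would be significant with probability about 57% to over 99%, so it could be read as better stability. If the fall is a constant shift, the probability is about 5% and the problem does not arise. The result rests on three assumptions that the document does not supply: the proportional pattern, the CV, and the SD of the paired difference in glucose SD. SD is not a wrong endpoint; it is insufficient alone for the conclusion that the Discussion announces.

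**What to change.** Keep SD as the listed secondary endpoint. Before database lock, pre-specify beside it the within-patient difference in CV, from the same CGM data and the same last 2 weeks, analysed with the same mixed model. State that any conclusion about more stable glucose will be drawn from the two together, with confidence intervals for both:

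- SD and CV both fall: more stable in absolute and in relative terms.
- SD falls, CV flat: compatible with a proportional drop in level.
- SD flat, CV rises: compatible with a constant shift.

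Align the Discussion's sentence on stability with this reading.

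The cost is a change of wording in the endpoint list and the analysis plan, which section 2.12 says will be signed before lock. No new measurement is needed. The downsides are one more reported measure and a more cautious stability claim. CV must not be interpreted alone, because it rises under a constant shift.
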